### Intervention group

Participants in the intervention group will receive EPO Feeding program and standard care. The EPO Feeding program is a 4-module intervention program focused on optimizing parental feeding practices. The components and contents of the EPO Feeding program are presented in Appendix 6. Two healthcare professionals in the Department of Child Health in the local maternal and child health hospital will be trained to deliver the EPO Feeding program. Before each module, they will pre-present the module to the researcher (JW) to ensure their presentation is in accordance with the EPO Feeding intervention manual via VooV Meeting, which will be recorded and sent to parents in the control group after all follow-ups. Considering the effectiveness and cost-effectiveness of the intervention [1], we will divide participants in the intervention group into two groups (15-18 parents per group) to attend the modules separately. Each weekly module will last 45-60 min in the kindergarten classroom, incorporating lesson/session (i.e., slides shows and handouts), group discussion, uptake of key messages, supplementary materials (e.g., stories, key messages and learning videos) to improve the acquisition of participants' knowledge, skills, and behaviors. Each module will take place twice every week (Friday: 12.30-13.30 PM; Saturday: 09.00-10.00 AM) at the kindergarten premises after receiving approval from the gatekeeper. Parents in the intervention group can choose one regular time to attend the module every week. After each module, homework activities will be assigned to participants to help reinforce their knowledge, skills, and behaviors. Participants will receive weekly messages via WeChat reminding them to attend the module with brief information. On the other hand, a WeChat group will be built to facilitate parental involvement, learning, and communication. The WeChat group will be monitored by two healthcare professionals in the areas of child health and nutrition. You can share your feelings, experiences, ideas or practices relevant to each module in the WeChat group. It is

completely voluntary but encouraged because other parents may find them helpful for their positive behavior change and two HCPs can provide feedback. All shared information in the WeChat group will not be used for any report/publication. Except for baseline assessment (T0), parents in the intervention group will receive text messages about their preschool child's actual weight status a week before the assessment of each time point from a kindergarten healthcare staff who is not involved in collecting child weight and height and is not blind to group allocation. Participants will also be informed that they could make contact via WeChat/phone call if they have related questions or concerns at any time. In addition, participants continue to receive infographics summarising the key points from each of the modules every week via WeChat group at the end of the program until the one-month follow-up.

#### Control group

Parents involved in the control group will receive standard care, including the printed materials of child health-related dietary recommendations published by Chinese government/Nutrition Society. These materials will also be distributed to the participants in the intervention group. After the final data collection at one-month follow-up, participants from this group will be offered the complete material package of the EPO Feeding program, a book (related to child eating) as a gift and their child's weight status measured at the final time point and provided access to pre-recorded modules by healthcare professionals as an incentive, but they will not be included in the WeChat group.

#### Data collection:

The schedule of enrolment, interventions, and assessments is shown in Appendix Figure 3.

##### - Quantitative data

Demographic and socioeconomic data including children's age, sex; caregivers' role, age, weight, height, education level and household annual income, and number of children will be collected at baseline only. A survey related to the trial acceptability will be assessed immediately after the intervention (Appendix 7). Quantitative data including parental feeding practices, perception of child weight, parenting sense of competence; and child eating behaviors will be collected from participants at three-time points: baseline (T0), immediately after the intervention (T1), and one month after the intervention (T2). The kindergarten healthcare staff who is unaware of participants' group allocation will be trained to distribute and collect the questionnaires and measure children's weight and height at each time point in the kindergartens. The questionnaire will take approximately 15 minutes.

The questionnaire also includes some identified information: preschool child student ID number, participant contact details (phone number). We need to assess child's actual weight and height at the kindergarten at each time point after getting the approval of kindergarten gatekeeper. Except for baseline assessment (T0), parents in the intervention group will receive text messages about their preschool child's actual weight status a week before the assessment of each time point from a kindergarten healthcare staff who is not involved in collecting child weight and height and is not blind to group allocation. We will also use child's actual weight status to compare with parental self-reported and visual perception of child's weight separately and then, we can calculate the prevalence of parental misperception of child's weight in this sample.

The included scales have been all used in the Chinese sample and showed moderate to good internal consistency reliability in existing studies including my previous study [2]. The questionnaire is attached in the additional file (Appendix 4 and 5).

##### - Qualitative data

After completion of modules, the participants will be sent an invitation for semi-structured interview via WeChat messages. If some participants drop out, the researcher (JW) will first send messages to them via WeChat and then ask if they could be interviewed online. If they agree, the semi-structured interview will be conducted after receiving their written informed consent. An interview indicative topic guide (Appendix 1) is informed by the objectives of feasibility and acceptability which will guide the qualitative data collection. Interviews will take place on the kindergarten premises or via phone/WeChat call and will last about 40 min. Two healthcare professionals in the local maternal and child health hospital where we will register our study will deliver the intervention program but will be included in the process evaluation (semi-structured interviews).

#### Data analysis

##### - Quantitative data analysis

The primary objectives of this feasibility and acceptability RCT will be addressed via descriptive estimates (e.g., means, standard deviations, and percentages). Measurements of study feasibility include recruitment rate, rates of intervention compliance, and participant retention rates. The total number of participants included in each attendance and assessment will be reported to account for missing data. The retention rate will be calculated as the rate of completion of one-month follow-up. The feasibility of collecting quantitative outcome data includes < 20% missing data at the group level at each time point. The acceptable proportion of enrolled participants who complete all modules will be 80% or greater, given that there's 10%-16% dropout rate of participants in some related RCTs [3,4, 5]. Participants will also rate five elements of the intervention on a 10-point Likert scale will be used to test the acceptability of the intervention. Participant acceptability of the intervention will be considered by a score of six or more, unacceptability will be regarded when participants scored five or less on the Likert scale.

Quantitative secondary objectives will be addressed using exploratory statistical analysis. Intention-to-treat (ITT) principles will be used for parametric data, with all participants analyzed in the group which they are randomized regardless of whether they attend all data collection time-points or complete the intervention. Multiple imputations by chained equations (MICE) will be adopted to impute missing values if cases with < 10% missing data at each data collection time-point because this procedure can use all available variables with complete information in the study [6]. Descriptive statistics were used to describe the participants' characteristics. The characteristics and all dimensions of outcomes (i.e., parental feeding practices, sense of competence, perception of child weight, and child eating behaviors) will be compared between the intervention group and control group using t-tests (for continuous variables) and chi-squared tests (for categories variables). In addition to the ITT analysis, the completers analysis will be conducted using linear mixed models, which include intervention participants who have completed at least 3 modules (>80% of intervention content) and comparison participants who attend all data collection time-points. The linear mixed model regression procedure will be used to test intervention effects on outcomes with continuous variables. The models will include the outcome measures as the dependent

variables, treatment condition (intervention versus control) as the fixed factor, and confounding factors (e.g., parental education level, children's sex, and age) as covariates. McNemar's Test will be used to test the intervention effect on change in the proportion of parental accurate perception of their preschooler's weight status. Statistical significance is set at  $P < 0.05$  (two-sided). SPSS Statistics 27.0 (IBM Corp, Armonk, NY, USA) will be used for data coding, cleaning, and analysis.

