### Randomization

The randomization will be performed by an independent researcher (XXW) not connected with either participant recruitment or data collection. After completing the baseline assessment, parents will be randomized and allocated to one of the conditions through a concealed computerized random number generator by randomization.com, with an equal allocation ratio (1:1). Selection bias will be minimized by ensuring all participants eligible and recruited have equal opportunity of being allocated to each study group and follow-up completed. Due to the nature of the study, only the research members who collect and analyze the data from participants can be masked to the randomization. At the follow-up data collection time points, child height and weight measurements, and follow-up questionnaires will be taken and distributed by a trained kindergarten healthcare staff blinded to group allocation. Unmasking will not occur until databases are closed, and the main analysis has been completed.

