**(1) Parents in this feasibility trial (including parents in the intervention and control group)**

As this is a feasibility study, a formal sample size calculation for between-group comparisons of a primary outcome is not appropriate. A sample size of between 25 and 50 is considered reasonable in a feasibility study, to be able to establish feasibility, estimate the difference in retention rates with accuracy, and attain an appropriate standardized effect size (0.15-0.3) [1, 2]. The target recruitment for this feasibility RCT will be 70 (i.e., 35 participants per group), allowing for a 20% loss to follow-up rate and for at least 56 participants to complete the study.

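### The under-10% limit on multiple imputation shuts out the missed visits the protocol plans for and conflicts with its promise to analyse every randomised parent

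*Protocol*

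**What the plan says.** All of the analysis text is in Protocol section B9, Data analysis, Quantitative data analysis.

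- **Scope of intention-to-treat.** The approach is tied to one kind of outcome, those the protocol calls parametric. For these it promises an analysis "with all participants analyzed in the group which they are randomized regardless of whether they attend all data collection time-points or complete the intervention".
- **Imputation.** The next sentence says that MICE "will be adopted to impute missing values if cases with < 10% missing data at each data collection time-point". It does not say whether the 10% counts items within a person or persons within the sample, and nothing is said about missingness above it.
- **Tests.** Outcomes are compared between arms by t-tests and chi-squared tests. McNemar's test is named for accurate weight perception. Linear mixed models are introduced for a completers analysis that is additional to the intention-to-treat analysis. A later sentence then names them, without that restriction, for intervention effects on continuous outcomes. The listed model terms are treatment and covariates.
- **Feasibility criterion.** "The feasibility of collecting quantitative outcome data includes < 20% missing data at the group level at each time point".
- **Dropout elsewhere.** The module-completion target is justified "given that there's 10%-16% dropout rate of participants in some related RCTs".

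Section C1 sets recruitment at 70, or 35 per group, "allowing for a 20% loss to follow-up rate and for at least 56 participants to complete the study".

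**The concern.** In a trial with two follow-ups, most lost information comes from parents who do not return a questionnaire at all. That is the case the intention-to-treat sentence promises to cover, and it is the case the imputation limit excludes. The protocol expects it to be common: its own loss allowance is twice the limit.

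The tests named for comparing the arms need an observed or imputed value at the visit concerned. If imputation is not allowed and no other method is assigned, the comparison falls back on whoever was seen. Only the intervention arm is asked to attend four modules and do homework, so loss could differ by arm and be related to motivation. A result labelled intention-to-treat would then carry that selection.

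A second gap sits in the same sentence. Tying intention-to-treat to parametric data leaves the categorical weight-perception outcome outside the promise.

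**Working it through.** **Inputs.** Target 70 (35 per group), 20% loss and 56 completers come from section C1. Dropout of 10%-16% in related trials, the under-20% feasibility criterion and the under-10% imputation limit come from section B9, Data analysis. Item counts come from the outcome descriptions in section B8.

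**1. The plan's own figure.** 56 / (1 - 0.20) = 70, and 70 x 0.80 = 56. The recruitment figure reproduces exactly. Expected loss is 70 x 0.20 = 14. At the cited rates it is 70 x 0.10 = 7 to 70 x 0.16 = 11.2, so about 7 to 11.

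**2. Limit read within a person.** Items per assessment:

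- feeding behaviour scale: 4 + 3 + 4 + 6 + 7 = 24
- food as a reward: 2
- weight perception, verbal and visual: 2
- parenting competence: 8 + 9 = 17
- child eating behaviour: 5 + 6 + 5 + 4 + 5 = 25

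The total is 70 items. Under 10% means at most 6 missing (6/70 = 8.6%; 7/70 = 10%). Adding height and weight gives 72 fields and at most 7 missing. A missed visit is 100% missing, so it never qualifies.

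**3. Limit read across the sample.** Fewer than 10% of 70 persons means at most 6. With X ~ Binomial(70, p), where losses are assumed independent between parents:

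| Loss rate p | Expected missing | P(X <= 6), imputation allowed |
|---|---|---|
| 10% | 7 | 0.44 |
| 16% | 11.2 | 0.055 |
| 20% (planned) | 14 | 0.008 |

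On this reading, a trial with 10% to just under 20% missing in each group meets the protocol's feasibility criterion and yet has imputation switched off.

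**4. Precision at T2 if only observed parents are compared.** With equal loss by arm, 35 x 0.80 = 28 per arm. For an unadjusted difference in SD units, SE = sqrt(2/n):

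- n = 35: sqrt(2/35) = 0.239
- n = 28: sqrt(2/28) = 0.267

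The ratio is sqrt(35/28) = 1.118, an increase of about 12%.

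**5. Bias.** The shift in the difference between arms is (share lost x stayer-leaver gap) in the intervention arm minus the same product in the control arm. The documents give no gap, so the size is unknown. As an illustration only, take a gap in the intervention arm alone. A gap of 0.5 SD at 20% loss gives 0.20 x 0.5 = 0.10 SD. Gaps of 0.3 to 0.8 SD give 0.06 to 0.16 SD. At 10%-16% loss, a 0.5 SD gap gives 0.05 to 0.08 SD. Equal loss with equal gaps in both arms gives zero.

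**The case against.** A reader might infer that anyone who misses a visit is dropped and that the trial reverts to a complete-case analysis. The text does not support that. No sentence excludes such parents; the inclusion sentence says the opposite, and the limit governs when MICE is used. A parent who misses only T2 still counts at T1, so the t-tests would be available-case at each visit.

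The strongest defence is the general mixed-model sentence. Section B9 sets three repeated measures. If that model is fitted to all of them for every randomised parent, likelihood estimation keeps those with partial data and needs no imputation, and the t-tests may then be partly a check of group comparability. This stands as a possibility. Against it, the model is first attached to completers as an addition to the intention-to-treat analysis, and no time term is listed. If the rescue is intended, the text has to say so.

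Three further points hold:

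- The 0.10 SD illustration rests on an assumed gap in one arm and lies well inside a standard error of 0.267 SD. The 0.15-0.3 effect size in section C1 is not a declared target effect to set it against, because that section calls a formal between-group calculation inappropriate.
- The primary objectives are descriptive and untouched, and numbers at each assessment will be reported, so loss will be visible.
- The detail of an imputation model may be left to a statistical analysis plan, and its absence is not at issue. The threshold is at issue, because the protocol itself fixes it.

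**Conclusion.** The conflict is real. Under either reading of the 10%, MICE as restricted cannot deliver the intention-to-treat analysis promised one sentence earlier: missed visits are never imputed on the first reading, and on the second are imputed with probability 0.008 at the planned loss.

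Unless the mixed model is the intention-to-treat analysis, the stated tests rest on those seen at each visit. At T2 that means about 28 per arm, a standard error about 12% larger than with complete data, and exposure to attrition bias whose size the documents do not allow anyone to state. These figures assume 20% loss, equal loss by arm for the 28, and independent losses for the binomial probabilities.

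The effect is confined to the exploratory secondary outcomes. This should be fixed, but it does not threaten the feasibility conclusions.

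**What to change.** 1. Delete the under-10% condition, or confine it to scoring a subscale when a few of its items are missing.
2. State that the intention-to-treat analysis of continuous outcomes is a likelihood-based linear mixed model on all randomised parents, using T0, T1 and T2, with time and group-by-time terms. Randomisation follows the baseline assessment, so every randomised parent should contribute. MICE by arm without the threshold is an acceptable alternative.
3. Replace the restriction to parametric data so that intention-to-treat also covers the categorical weight-perception outcome.
4. Keep the completers analysis separate, and report available-case results as a sensitivity analysis.

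The cost is a change of wording and modest extra programming; no added participants or data collection are needed. Neither method recovers all of the lost precision or removes selection that the observed data do not explain, so numbers missing by arm and visit should still be shown.

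### The mixed model that tests intervention effects is introduced only for a completers set chosen after randomisation, leaving all randomised parents without a clearly assigned effect analysis

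*Protocol*

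**What the plan says.** All of this stands in B9 of the protocol.

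- **Status.** The primary objectives, feasibility and acceptability, "will be addressed via descriptive estimates (e.g., means, standard deviations, and percentages". For potential effects, "Quantitative secondary objectives will be addressed using exploratory statistical analysis". One threshold covers every test: "Statistical significance is set at $P < 0.05$ (two-sided").
- **ITT.** Intention-to-treat principles are to be used, with everyone kept in the allocated group. No effect model is named in that sentence.
- **t-tests.** Participant characteristics and the outcome dimensions "will be compared between the intervention group and control group using t-tests (for continuous variables) and chi-squared tests (for categories variables"). Neither a visit nor an analysis set is given. The listed outcomes are feeding practices, sense of competence, perception of child weight and child eating behaviours. BMI Z-score is not listed.
- **Completers.** "In addition to the ITT analysis, the completers analysis will be conducted using linear mixed models". Intervention parents enter this set with at least 3 modules; control parents enter it by attending every data collection point.
- **Effect test.** "The linear mixed model regression procedure will be used to test intervention effects on outcomes with continuous variables". This sentence names no analysis set. The model has treatment as its only listed fixed factor, plus covariates such as the parent's education and the child's sex and age.
- **Visits.** Outcomes are collected at "baseline (T0), immediately after the intervention (T1), and one month after the intervention (T2").

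**The concern.** The covariate-adjusted model is the stronger analysis and the one described as testing intervention effects. The only set named when it is introduced is the completers. Membership of that set is decided after allocation, and partly by the intervention itself, because only intervention parents have modules to attend. A comparison restricted in this way is no longer a comparison of randomised groups.

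At stake is the answer to the second objective, the potential effects of the programme. Followed as worded, the adjusted estimate would describe engaged intervention parents against fully observed control parents, and the randomised comparison would get an unadjusted test or none. The Randomization text also holds unmasking until a main analysis is finished, but the protocol does not say which analysis that is.

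**Working it through.** **1. The plan's own figure.** C1 gives 70 parents (35 per arm), 20% loss and at least 56 completing. 56 / (1 - 0.20) = 70 and 70 x 0.80 = 56, or 28 per arm. This reproduces.

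**2. The sentences side by side.**

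| Sentence | Set named | Method | Visit |
|---|---|---|---|
| ITT principles | all randomised | none named for effects | none |
| t-test / chi-squared | none | unadjusted comparison | none |
| Completers | completers | linear mixed model | none |
| Intervention effects | none | linear mixed model | none |
| Model contents | none | treatment plus covariates | no visit term |

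**3. The possible readings.**

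- (a) Literal: the t-tests are the ITT comparison and the mixed model is the completers analysis. The randomised set gets the unadjusted test.
- (b) The t-tests are a baseline table and the mixed model is still the completers analysis. The randomised set has no clearly assigned test of effect.
- (c) The intervention-effects sentence is general and covers ITT and completers alike. The problem disappears.

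Only (c) keeps the main estimate randomised, and nothing in the text selects it.

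**4. The two entry rules differ.** An intervention parent who attended 2 modules and returned every questionnaire is left out; control parents face no module condition. An intervention parent with 3 modules who missed T2 is kept; a control parent who missed T2 is left out.

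**5. How large could the selection effect be?** This is an illustration, since the documents give no figure for it. Suppose a share p of an arm qualifies, on a normally distributed tendency to qualify that correlates r with the outcome. The mean of those who qualify is then shifted by r x phi(z) / p standard deviations, where phi is the normal density and z is the normal quantile of p.

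- With p = 0.80 (in line with the 20% loss in C1): z = 0.842, phi(z) = 0.280, and 0.280 / 0.80 = 0.35.
- If both arms retain 80%, the net bias is 0.35 x (r in intervention - r in control).
- r = 0.3 in the intervention arm and 0 in control: 0.35 x 0.3 = 0.105 SD.
- The same r in both arms: 0.

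C1 cites a standardised effect of 0.15-0.3. Against that, 0.105 is 0.105 / 0.3 = 35% to 0.105 / 0.15 = 70%.

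**6. What the model returns.** With treatment as the only listed fixed factor and no visit or treatment-by-visit term, the model gives one coefficient averaged over whichever visits enter. If T0 is among them, an effect d that is equal at T1 and T2 appears, in balanced data, as (0 + d + d) / 3 = 2d/3. Differences at T1 and T2 cannot be read from it separately.

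**The case against.** The best defence is that the paragraph can be read coherently. The t-test sentence follows the one on descriptive statistics, opens with participant characteristics, names no visit and omits BMI Z-score, which is an outcome in the second objective. That fits a baseline table. The ITT principle opens the account of the secondary objectives, the intervention-effects sentence carries no restriction to completers, and the completers analysis is presented as an addition. This stands as a possible reading, and it is why the point is about wording that must be settled and not about a proven restriction. It does not dispose of the point. The model is first attached to completers, its contents follow directly on that definition, and no sentence assigns it to all randomised parents.

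It can also be said that naming a deciding visit or ranking sensitivity analyses belongs in a statistical analysis plan. That is largely right for an exploratory objective, and no finding is made of it. Which set the effect model is fitted in is different, because the protocol has already worded that, and worded it badly.

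A reader might go further and infer that each continuous outcome faces two competing tests, so that the false-positive rate is inflated. In a simulation with 35 per arm, 28 + 28 completers drawn at random, T1-T2 correlation 0.5-0.7 and covariates explaining 10-30% of variance, at least one of a T1 t-test, a T2 t-test and the completers model was significant in about 11-12% of trials with no true effect. The T2 t-test and the completers model disagreed in about 16-34% of trials at 0.3-0.5 SD. The documents do not support presenting these as consequences of the plan. It never says the t-tests are run at T1 or T2, or that either result would count; BMI Z-score is not in the t-test list; and some disagreement between a main and a sensitivity analysis is ordinary. Nor do these figures size the selection problem, because the completers there were drawn at random.

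**Conclusion.** The point holds as a defect of wording with a real consequence if followed literally: the adjusted estimate of intervention effect would come from a subset selected after randomisation by unequal rules, and the randomised set would have at most an unadjusted t-test at an unstated visit. The 0 to 0.105 SD in the working rests on assumed values (80% qualifying, correlation 0 to 0.3 in the intervention arm, none in control). It shows that the bias can matter beside an effect of 0.15-0.3; it does not predict it.

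The weight is moderate. The effect analyses are exploratory, and the feasibility and acceptability verdicts are descriptive and unaffected. A reader might infer that decisions on the programme or a full trial hang on these tests. The protocol ties refinement of the programme to the feasibility and acceptability objective (B5), and preparation for a full trial to the qualitative process evaluation (B8). It attaches no progression rule to any P value.

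**What to change.** In B9, Quantitative data analysis:

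- State that the linear mixed model is fitted in all randomised parents as allocated, using T0, T1 and T2 with visit and treatment-by-visit terms, so that the between-arm differences at T1 and T2 can be estimated.
- State that this is the analysis of intervention effect for every continuous outcome, including BMI Z-score.
- Keep the same model in completers as a supplementary sensitivity analysis.
- Do not use the t-tests as tests of outcome effect; describe baseline by arm.

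The cost is a change to one paragraph, with no new data or participants and fewer tests to run. The small downside is that the completers results become supportive only.

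### The supplementary completers analysis selects each arm by a different rule, labels 3 of 4 modules as more than 80% of content, and leaves the mixed model's population unclear

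*Protocol*

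**What the plan says.** The secondary objectives are handled in Section B9, Quantitative data analysis, as exploratory work. Under intention to treat (ITT), the protocol has "all participants analyzed in the group which they are randomized regardless of whether they attend all data collection time-points or complete the intervention". Arms are then compared with t-tests for continuous and chi-squared tests for categorical variables. Next comes a second analysis: "In addition to the ITT analysis, the completers analysis will be conducted using linear mixed models". Its population is "intervention participants who have completed at least 3 modules (>80% of intervention content) and comparison participants who attend all data collection time-points". The following sentence says that a linear mixed model will test intervention effects on continuous outcomes. It adds treatment condition and covariates but names no analysis population.

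Section B9, Intervention group, gives the denominator for the module rule: "The EPO Feeding program is a 4-module intervention program focused on optimizing parental feeding practices". On length it says: "Each weekly module will last 45-60 min in the kindergarten classroom".

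**The concern.** Three things in this short stretch of text do not fit together.

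- **Different filters.** One arm is selected on how much of the programme parents took up, the other on whether they came to every assessment. Both happen after randomisation and they are different behaviours. If either is related to how a parent would have scored anyway, the arms can differ with no programme effect.
- **A percentage that does not match its rule.** An analyst who follows the module count and one who follows the percentage would build different analysis sets.
- **An unclear home for the mixed model.** The model is named in the completers sentence, and the sentence that describes it gives no population. The covariate-adjusted estimate, tested at the two-sided 5% level, could therefore come from the filtered subset.

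Testing potential effects is a stated objective (Section B5), so these estimates are likely to inform a later trial.

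**Working it through.** **Inputs.** Four modules of 45-60 minutes (Section B9, Intervention group). Completer rule of at least 3 modules, glossed as more than 80% of content (Section B9, Quantitative data analysis). 35 parents per arm, 20% loss, and a cited standardised effect range of 0.15-0.3 (Section C1). Attendance probabilities, retention fractions and correlations in steps 2 and 4 are assumptions; the protocol gives none.

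**Step 1: the stated percentage.**
- By count: 3/4 = 75%.
- By contact time, highest case (three 60-minute modules attended, a 45-minute one missed): 3×60 / (3×60 + 45) = 180/225 = 80.0%.
- By contact time, lowest case: 3×45 / (3×45 + 60) = 135/195 = 69.2%.

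The figure of more than 80% is not reproduced by either measure. Only 4/4 = 100% exceeds it. The 80% in the feasibility criterion does not explain it, because that is a proportion of participants (those completing all modules), not a share of content.

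**Step 2: what depends on the reading.** If each module is attended independently with probability p, then P(at least 3) = 4p³(1−p) + p⁴ and P(all 4) = p⁴. At p = 0.90 these are 0.2916 + 0.6561 = 0.948 and 0.656. Multiplied by 35:

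| p (assumed) | at least 3 modules | all 4 modules |
|---|---|---|
| 0.80 | 28.7 | 14.3 |
| 0.85 | 31.2 | 18.3 |
| 0.90 | 33.2 | 23.0 |
| 0.95 | 34.5 | 28.5 |

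**Step 3: the two inclusion rules side by side.**

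| Parent | Intervention arm | Control arm |
|---|---|---|
| Misses an assessment | kept if at least 3 modules | removed |
| Low engagement, attends every assessment | removed if fewer than 3 modules | kept |

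If the 20% loss in Section C1 fell evenly, 0.20 × 35 = 7 controls would be removed. Intervention parents with the same missing assessment would stay, provided they attended 3 modules. A mixed model does not need that exclusion, since it can use incomplete repeated measures.

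**Step 4: illustration with no true effect.** Suppose a normally distributed trait governs retention, a fraction P with the highest values is kept, and the trait correlates ρ with the outcome. The retained mean then shifts by ρ·φ(z₁₋ₚ)/P in SD units. For P = 0.80 and ρ = 0.3 this is 0.3 × 0.280/0.80 = 0.105. The spurious difference is the intervention shift minus the control shift:

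| P (interv. / control) | ρ (interv. / control) | difference, SD |
|---|---|---|
| 0.80 / 0.80 | 0.3 / 0.3 | 0.000 |
| 0.80 / 0.80 | 0.3 / 0 | 0.105 |
| 0.70 / 0.90 | 0.3 / 0.3 | 0.091 |
| 0.70 / 0.90 | 0.3 / 0.1 | 0.130 |
| 0.60 / 0.80 | 0.5 / 0.1 | 0.287 |

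All these scenarios make the intervention filter at least as strong as the control filter. Exchanging the arms reverses the sign.

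**Step 5: the mixed model's population.** The text runs in this order: ITT principle, t-tests and chi-squared tests, completers analysis by mixed model, then the mixed model described without a population. It fits two readings: the model is run on completers only, or on the ITT set as well.

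**The case against.** The strongest reply is about weight. The completers analysis is supplementary, the ITT analysis keeps everyone as randomised, and the outcomes are exploratory. Section C1 says that a formal sample size calculation for a between-group comparison is not appropriate here. Any completers analysis conditions on behaviour after randomisation, so unequal rules are not the sole problem. All of this stands. A reader might infer that the trial's randomisation is compromised; the documents do not support that, because the loss of protection is confined to this one comparison.

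A reader might also infer that the ITT set gets only t-tests. That goes too far. The sentence describing the mixed model names no population and may be meant to cover the ITT set. What stands is an ambiguity.

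On the percentage, the protocol speaks of content, not modules or minutes. Module contents are in Appendix 6, which is not among the documents at hand, and the programme includes homework, messages and a WeChat group. An unequal weighting that exceeds 80% cannot be ruled out, so it would be too strong to call the figure impossible. Nothing in the protocol supports such a weighting, however. It is also fair that at least 3 modules reads as the operative rule, with the percentage as a gloss.

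On size, selecting controls on full attendance may also favour motivated parents and offset the bias, which is why the range starts at 0. With 28 completing per arm, the standard error of a simple standardised difference is about √(2/28) = 0.27 SD, comparable to the top of that range. This limits how much the result could be trusted in any case, but it does not justify different filters in the two arms.

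**Conclusion.** The point holds as a should-fix. Two parts rest on the text and simple arithmetic: the inclusion rules differ by arm, and 3 of 4 modules is 75% by count and no more than 80.0% by stated contact time. The third part is an ambiguity about where the mixed model is run.

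The size of any bias is unknown. The range of 0 to about 0.29 SD depends wholly on assumed retention and correlations, and the sign depends on which filter is stronger. It can be set beside the 0.15-0.3 cited in Section C1, but a reader should not take that range as a target effect: it appears there only to justify a feasibility sample size. The numbers of qualifying parents in step 2 likewise rest on assumed independent attendance. The primary feasibility and acceptability objectives, which are descriptive, are unaffected.

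**What to change.** 1. State that the linear mixed model is run on all randomised participants, and that this is the main exploratory analysis of effect.
2. Correct the completer label to at least 3 of 4 modules (75%). If more than 80% is really meant, reconcile it with the 3-module rule and say how content is measured.
3. Either apply the same assessment-attendance condition to both arms and label the completers result a non-randomised sensitivity analysis, or report completers descriptively without a test.

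A complier-average effect with allocation as instrument would not be a sound replacement. It requires allocation to act only through attending at least 3 modules. Intervention parents also receive weight-status texts, the WeChat group and weekly infographics, with no attendance condition stated (Section B9, Intervention group).

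The cost is a few sentences in one section. No further data or participants are needed, and at most the mixed model is fitted to one more population.
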